#### Health economic assessments

If a significant effect of metformin on the primary outcome is observed, cost-effectiveness and cost-utility analyses will be performed. These evaluations will adopt a health system perspective, including estimates of all healthcare costs, particularly those relating to drugs, doctors’ visits and in-patient charges and costed using standard country-specific list prices. The cost-effectiveness analysis will produce an incremental cost-effectiveness ratio defined as a cost per AAA event avoided. For the cost-utility analysis, health utility scores will be generated for each participant by converting responses to the SF-36 into a single SF-6D score using validated algorithms and applying country-specific utility weights where available; weights currently exist for the UK and Australia. Each year participants will be asked how many outpatient appointments they have attended, and specifically how many of those appointments were related to their AAA. These analyses will generate costs per quality-adjusted life year (QALY) gained (or lost) and include sensitivity analyses, particularly around using pooled or country-specific data for each cost-utility analysis. Country-specific thresholds for determining cost-effectiveness will be used where available and presented in combination with cost-effectiveness acceptability curves.

### Adjudication

An independent adjudication committee, blinded to study treatment assignment, will adjudicate all potential primary outcome events as well as myocardial infarction, stroke and all-cause mortality.

### Participant timeline {13}

A summary of all study assessments is presented in Table 1.

**Table 1 Tab1:** Schedule of evaluations

Visit	Screening −10 to −6 weeks	Run-in^**a**^ −6 to 0 weeks	Randomisation 0 weeks	Follow-up^**b**^			
				3 monthly	6 monthly	Annually	Final^**c**^
Time window for evaluation	N/A	+ 2 days	N/A	±14 days	±14 days	±14 days	N/A^c^
Informed consent (prior to or at screening)	X						
Assessment of eligibility	X						
Demographics	X						
Anthropometrics—height and weight	X					X^f^	X^f^
Behavioural—smoking	X						
Medical history	X						
Concomitant medications	X					X	X
AAA imaging (standard care)^h^	X					X	X
Blood tests—creatinine, eGFR, HbA1c, CRP (if available), LDL-C (if available)^d^	X					X^g^	X^g^
Blood sample for biomarker sub-study^e^	X					X^e^	X
QoL questionnaires: SF-36, AneurysmDQoL	X					X	X
Run-in medication dispensed	X						
Randomisation			X				
Study medication dispensed			X		X	X	
Study medication adherence		X		X	X	X	X
AESI reporting		X		X	X	X	X
Serious adverse event reporting		X		X	X	X	X
Assessment of exploratory outcomes not classified as SAEs (diagnosis of cancer, diagnosis of diabetes, symptomatic gout)				X	X	X	X
Health economic assessment questions						X	X

^a^Participants will be contacted by telephone fortnightly during the 6-week run-in period

^b^Participants will be contacted every 3 months after randomisation

^c^Participants will undergo a final follow-up within 3 months of the date of the last adjudicated primary outcome event

^d^If blood tests are available from within 6 months prior to screening, no need to repeat tests at screening

^e^Only for participants who have consented to the biomarker sub-study. Samples will be collected at entry, at years 1 and 3, and at the final scheduled follow-up

^f^Weight only

^g^eGFR only. If blood tests are available from within 3 months prior to annual follow-up/final follow-up, no need to repeat tests

^h^If imaging is available within 12 months of screening/annual follow-up, no need to repeat tests

### Sample size {14}

While the trial is outcome event driven (an estimated 616 primary outcome events are needed), a sample size estimate has considered the likely participant numbers needed. The planned sample size is 1954 (metformin *n* = 977; placebo *n* = 977) which will provide 90% power (*p* = 0.05) to detect a 25% or greater reduction in the relative risk of the primary outcome with metformin compared to placebo over a mean follow-up of 3.5 years. This calculation was based on:
A 25% relative risk reduction for the primary outcome which is less than reported by observational studies comparing AAA events between patients who were, or were not receiving metformin [42]An AAA repair or rupture rate of 9% per annum (31% over 3.5 years) in the control group has been assumed to accrue a total of 616 primary endpoint events in the trial. This event rate is lower than the occurrence of AAA repair or rupture in our prospective registry (AAA events observed at 12% per annum) [42] and less than that reported in a number of small AAA trials [2, 43]. For example, the UK small aneurysm trial and the surveillance versus aortic endografting for small aneurysm (CAESAR) trial reported 3-year rates of AAA rupture or repair of 52% and 61%, respectively [43]A drop-out rate of 5% per annum (discontinuation of metformin in the intervention group) which is expected to be minimised by the active run-in periodA drop-in rate of 1% per annum (commencement of metformin in the control group) which is expected to be low because incident diabetes will be uncommon and options for use of therapy based on agents other than metformin will be discussed with participants and their responsible physician

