**Methods:**

MAT is an international, multi-centre, prospective, parallel-group, randomised, placebo-controlled trial. Participants must have an asymptomatic AAA measuring at least 35 mm in maximum diameter, no diabetes, no contraindication to metformin and no current plans for surgical repair. The double-blind period is preceded by a 6-week, single-blind, active run-in phase in which all potential participants receive metformin. Only patients tolerating metformin by taking at least 80% of allocated medication will enter the trial and be randomised to 1500 mg of metformin XR or an identical placebo. The primary outcome is the proportion of AAA events defined as rupture-related mortality or need for surgical repair. Secondary outcomes include AAA growth, major adverse cardiovascular events and health-related quality of life. In order to test if metformin reduced the risk of AAA events by at least 25%, 616 primary outcome events will be required (power 90%, alpha 0.05).

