### Assignment of interventions: allocation

#### Sequence generation {16a}

A random sequence for study arm allocation will be generated by the trial statistician prior to commencement. Randomisation will be conducted using a secure Web-based system and will be stratified by study centre, sex and AAA diameter (35–38.9, 39–42.9, 43–46.9 and ≥ 47 mm) on imaging. Randomisation will be blocked in a 1:1 ratio.

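### The sample-size section reaches 616 events from 1954 participants in 3.5 years only by giving both arms the control rate; with the planned 25% reduction the count is 10–14% lower and 616 takes at least about 4 years

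*Protocol article*

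**What the plan says.** All the figures are in the protocol article, mostly under Sample size {14}.

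- The trial is event driven: "an estimated 616 primary outcome events are needed". The Methods paragraph of the abstract says the same: "616 primary outcome events will be required (power 90%, alpha 0.05").
- "The planned sample size is 1954", 977 per arm, for 90% power "to detect a 25% or greater reduction in the relative risk of the primary outcome with metformin compared to placebo". The duration attached to that claim is a mean of 3.5 years.
- Events are projected from the control arm alone: a rate of "9% per annum (31% over 3.5 years) in the control group has been assumed to accrue a total of 616 primary endpoint events". No metformin-arm rate or pooled rate is given.
- Two dilution inputs are listed: "A drop-out rate of 5% per annum (discontinuation of metformin in the intervention group"), and drop-in to metformin in the control group at 1% per annum.

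Allocation is 1:1 (Sequence generation {16a}). The primary analysis is an intention-to-treat Cox model reporting a hazard ratio (Statistical methods {20a}). Table 1 places each participant's final visit within 3 months of the last adjudicated primary event. Trial design {8} expects a mean of 3.5 years on study medication.

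**The concern.** A trial designed to detect a 25% reduction should project its events from two different arm rates. Here the stated total is what one gets when both arms run at the control rate. The sample size, mean follow-up and event target are then inconsistent under the effect the trial is designed to find.

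What is at stake is mainly duration. If the trial waits for 616 events, it runs longer than the stated mean of 3.5 years, and with 5% per annum stopping metformin, longer follow-up weakens the intention-to-treat contrast. If follow-up were instead held to 3.5 years, the event target would be missed and, on some readings of the assumptions, so would 90% power.

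**Working it through.** **Inputs from the protocol article.** N = 1954 (977 per arm); control rate 9% per annum, given as 31% over 3.5 years (0.09 × 3.5 = 31.5%); 25% reduction; 90% power; drop-out 5% and drop-in 1% per annum. Two-sided alpha of 0.05 is my assumption, in line with the 95% confidence interval.

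**1. The plan's event total.** 1954 × 0.09 × 3.5 = 615.5. Conversely, 616 / 0.315 = 1956, close to the planned 1954. The link works only with the control rate in both arms.

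**2. Is 616 sensible as a required count?** Schoenfeld: D = 4(1.960 + 1.2816)² / (ln HR)².
- HR 0.75: D = 508 (Freedman's formula gives 515).
- HR 0.77: D = 615.3, rounded up to 616.

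So 616 matches a 25% effect diluted to a net HR of about 0.77. Freedman's 515 divided by 0.95^3.5 also gives 616.3. The target can be explained without the control rate.

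**3. Expected events with the 25% reduction, 31–31.5% in control.**
- 977 × 0.31 × (1 + 0.75) = 530.
- 977 × 0.315 × 1.75 = 539.
- With the 25% as a hazard ratio and full adherence: 540–549.
- With the stated drop-out and drop-in: 545–554. This uses constant hazards, with those who cross over taking the other arm's hazard.

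The shortfall against 616 is 62–86 events: 62/616 = 10%, 86/616 = 14%.

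**4. If 9% compounds.** As a hazard, 1 − exp(−0.315) = 27.0%. As an annual risk, 1 − 0.91^3.5 = 28.1%. With HR 0.75 the count is 470–489 under full adherence and 473–493 with drop-out and drop-in.

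**5. Mean follow-up needed for 616 events with N = 1954.**
- 9% per person-year at risk: 616 / (977 × 0.09 × 1.75) = 4.0 years.
- Across the 31–31.5% readings: about 4.0–4.2 years.
- If 9% compounds, with drop-out and drop-in: about 4.6–4.8 years.

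**6. Power if follow-up ended at 3.5 years.**

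| Reading of the 25% | 31–31.5% in control | 27–28% in control |
|---|---|---|
| HR 0.75, no dilution | 91–92% | 87–89% |
| HR 0.75 on treatment, diluted by stated drop-out and drop-in (net HR about 0.772–0.773) | 85–86% | 80–82% |
| Ratio of cumulative risks 0.75, undiluted | 97% | 94–95% |
| Ratio of cumulative risks 0.75, diluted (31% in control) | about 94% | not computed |

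**7. Power when 616 events are reached.** Drop-out continues to accumulate. In the diluted model the net HR is about 0.775 at 4.0–4.1 years and 0.78 at 4.6–4.8 years. At those values, 616 events give about 88–89% and 87% power respectively. Reaching 90% would take about 650 and 670–680 events.

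**The case against.** The best defence is that the trial is driven by events, not by the calendar. The 616 is the binding figure, the sample size is introduced as an estimate of likely numbers, and the final visit is tied to the last primary event. A reader might infer that the trial will stop at 3.5 years underpowered; no stopping rule in the article says so. This part stands, and it makes longer follow-up the main consequence.

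A reader might also infer that 616 is merely the control rate multiplied out, and so has no basis as a target. Step 2 shows otherwise: it is a credible requirement for a diluted effect.

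Power need not fall below 90%. At 530–554 events an undiluted HR of 0.75 has 91–92%, and the article words its target as a relative risk, which read cumulatively gives more. That stands as a limit on the power claim. Against it, the article lists drop-out and drop-in among the bases of its calculation and analyses by intention to treat with a Cox model. An undiluted HR of 0.75 would also need only about 508–515 events, which leaves 616 unexplained.

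The compounding point is a reading too. If 9% is per person-year and 3.5 years is mean time at risk, 31.5% events per participant is exact.

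Finally, the article calls 9% conservative against 12% per annum in the sponsor's registry, and its Discussion concedes that the rate could vary. At 12% per person-year the count would be 977 × 0.42 × 1.75 = 718. A higher true rate could hide the error in practice, but the shortfall arises at exactly the rate the article chose to plan on.

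**Conclusion.** The inconsistency is real and is wrong as written. Under the article's own control rate and 25% reduction, 1954 participants followed for a mean of 3.5 years are expected to give about 530–554 events, 10–14% short of 616; if 9% compounds, about 470–495. The fault lies in the step from sample size and follow-up to events, not in the 616.

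The firm consequence is duration: about 4.0–4.2 years mean follow-up (about 4.6–4.8 if 9% compounds). A plain statement that the trial lacks 90% power is not supported. It falls to about 85–86% at 3.5 years (80–82% if 9% compounds) only when the 25% is an on-treatment hazard ratio diluted by the stated drop-out and drop-in; on that same reading, waiting for 616 events gives about 87–89%.

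These figures assume two-sided alpha, constant hazards and no loss to competing death or withdrawal. The article gives no rate for those losses; any would lower the count further.

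**What to change.** Keep the sample size and the event-driven stop, and rewrite the sample-size paragraph so that it:

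- projects events from the sum of the two arms' rates, not the control rate applied to everyone;
- says whether 9% is per person-year at risk or an annual risk, and makes the 3.5-year figure consistent with that (31.5 events per 100 participants for 3.5 years at risk, or 27–28% if it compounds);
- states the net hazard ratio that 616 events detect with 90% power, about 0.77;
- gives the expected events at 3.5 years, the expected mean follow-up to reach 616, and the power with dilution evaluated at that longer follow-up (about 87–89%).

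The expected 3.5 years on study medication in Trial design {8} should then be brought into line with the revised forecast. The work is rewording and a new projection, with no extra participants. The cost is that the stated duration or power becomes less favourable.

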### Trial design {8}

MAT is an international, multi-centre, prospective, parallel-group, randomised, double-blind, placebo-controlled phase 3b trial. The double-blind period will be preceded by a 6-week, single-blind (participants are blinded), active run-in phase in which all potential participants receive metformin XR with fortnightly dose up-titration (Fig. 1). The aim of this run-in phase is to promote the randomisation of participants who tolerate the treatment regimen and to increase the likelihood of high treatment adherence during long-term follow-up. It is anticipated that randomised participants will receive study medication for a mean of 3.5 years. All participants will be asked to continue the study drug until the trial is completed.

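### The 616 events forecast from 1954 participants at a mean of 3.5 years leave out the assumed benefit of metformin; the protocol's own inputs give about 530 to 555, so reaching 616 takes longer follow-up than stated

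*Protocol article*

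**What the plan says.** In the protocol article, Sample size {14} opens with the event target: "While the trial is outcome event driven (an estimated 616 primary outcome events are needed". It then turns to participant numbers: "The planned sample size is 1954", 977 per arm, which is said to give 90% power over a mean follow-up of 3.5 years. Sequence generation {16a} confirms equal allocation: "Randomisation will be blocked in a 1:1 ratio".

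The listed assumptions include "A 25% relative risk reduction for the primary outcome", discontinuation of metformin in 5% per annum of the intervention group, and metformin being started in 1% per annum of controls. The event rate is 9% per annum, given as 31% over 3.5 years, and this rate "in the control group has been assumed to accrue a total of 616 primary endpoint events in the trial".

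The abstract gives the same target: "616 primary outcome events will be required (power 90%, alpha 0.05". Footnote c of Table 1 ties the final follow-up to the date of the last adjudicated primary event.

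**The concern.** The number 616 does two jobs. It is the number of events the analysis requires, and it is the number that 1954 participants are expected to produce in a mean of 3.5 years. The second use rests on a rate described as belonging to the control group. Half the participants are assumed to have a 25% lower risk, so the total for the whole trial should fall below the control rate multiplied by everyone.

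If the forecast is too high, then 616 events, 1954 participants and 3.5 years cannot all hold when metformin works as assumed. Either follow-up runs past the stated mean, or a trial of 3.5 years yields fewer events than the stated requirement.

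**Working it through.** **Inputs, all from Sample size {14}.** 977 per arm; control rate 9% per annum, 31% over 3.5 years; 25% relative reduction; mean follow-up 3.5 years; 5% per annum drop-out on metformin; 1% per annum drop-in on control; 616 events; 90% power; alpha 0.05. The article does not give the sidedness of alpha, so two-sided is assumed. It affects power but not event counts.

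**1. Reproducing the forecast.** 1954 × 0.09 × 3.5 = 615.5, which rounds to 616. The rounded 31% gives 1954 × 0.31 = 606, so the match needs the unrounded 31.5%. No other combination of stated inputs that was tried gives 616 from 1954.

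**2. Is 616 plausible as a requirement?** For HR 0.75, Schoenfeld's formula gives 4 × (1.960 + 1.282)² / (ln 0.75)² = 508 events, and Freedman's gives 515. With 5% per annum stopping, on average 0.05 × 3.5 / 2 = 8.75% are off drug. Dividing by 0.9125² gives 610 and 618. So 616 is plausible as a required number.

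**3. Arm-specific total, no crossover.**
- 25% as a risk ratio: 977 × p × 1.75 = 530 (p = 31%) or 539 (p = 31.5%).
- 25% as a hazard ratio: 977 × [p + 1 − (1 − p)^0.75] = 540 or 549.

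**4. With the stated crossover.** Assume a constant control hazard λ = −ln(1 − p)/3.5, which is 0.1060 or 0.1081 per year. The hazard is λ × HR while on metformin and λ while off it. Participants stop at 0.05 per year in the metformin arm and start at 0.01 per year in the control arm. A risk ratio of 0.75 corresponds to HR = ln(1 − 0.75p)/ln(1 − p) = 0.71. Everyone is followed for the same time, and competing death is ignored. Power is Φ(½ × √events × |ln HR| − 1.96), using the average HR over follow-up.

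Each pair below is for p = 31% / 31.5%.

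| 25% read as | Crossover | Average HR | Events at 3.5 years | Years to 616 | Power at 3.5 years |
|---|---|---|---|---|---|
| Risk ratio | none | 0.71 | 530 / 539 | 4.19 / 4.11 | 97% / 98% |
| Hazard ratio | none | 0.75 | 540 / 549 | 4.10 / 4.02 | 92% / 92% |
| Risk ratio | 5% / 1% | 0.74 | 535 / 544 | 4.14 / 4.06 | 94% / 94% |
| Hazard ratio | 5% / 1% | 0.77 | 545 / 554 | 4.05 / 3.98 | 85% / 86% |

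The shortfall runs from 616 − 554 = 62 to 616 − 530 = 86 events, or 10–14% of 616. Crossover does not close the gap, because drop-out raises the metformin risk only to about 24–25%.

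**5. What 616 at 3.5 years would need.** With a risk ratio of 0.75, the control risk would have to be 616 / (977 × 1.75) = 36.0%, not 31%.

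**6. Sensitivity to the control risk.** Compounding 9% per annum gives 1 − 0.91^3.5 = 28.1%. Treating 0.09 as a hazard gives 1 − e^(−0.315) = 27.0%. At HR 0.75 the total is then about 470–493 events with or without crossover, and 616 is reached at about 4.5–4.8 years. Power at 3.5 years would be about 88–89% for a net HR of 0.75 and about 80–82% with crossover.

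**The case against.** The strongest reply is that the trial is event driven. Sample size {14} calls 616 an estimate and offers 1954 as a guide to likely numbers. Table 1 ties the last visit to the last primary event, and Trial design {8} asks participants to stay on study drug until the trial is completed. If events come more slowly, follow-up lengthens and power at 616 events is kept. This stands. It limits the consequence, but it does not make the forecast right.

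Three stronger readings are tempting, and the document does not support them.

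- **The trial is underpowered.** Nothing fixes closure at 3.5 years. Even if follow-up were so limited, with a control risk of 31–31.5% power falls below 90% only when the 25% is an on-treatment hazard ratio diluted by crossover.
- **Drug supply or an end date is set wrongly.** Kits cover six months at a time, and Trial status dates only the end of recruitment. Nothing derives supply or closure from 3.5 years.
- **Time on drug is misstated.** Trial design {8} expects that "randomised participants will receive study medication for a mean of 3.5 years", and 5% per annum stopping might seem to contradict this. The statement is an expectation. At a mean follow-up of 4.0–4.2 years, (1 − 0.95^T)/(−ln 0.95) gives about 3.6–3.8 years on drug, so no downward correction follows.

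Two further objections stand in part. The article does not say how 616 was built, so the mechanism is an inference; the mismatch with the stated inputs does not depend on it. The Discussion also admits that the event rate could vary, and the sample size section cites a registry rate of 12% per annum. That is uncertainty about the control rate, which is a different matter from leaving the assumed treatment effect out of the total.

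**Conclusion.** The forecast of 616 events is wrong as written. Under the protocol's own 25% reduction and 31–31.5% control risk, 1954 participants yield about 530–555 events at a mean of 3.5 years: 530–549 without crossover and 535–554 with it. The target is reached at about 4.0–4.2 years.

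These totals are conditional on accepting 31–31.5% at 3.5 years, a constant hazard, equal follow-up and no competing death. Compounding 9% per annum widens the gap. Competing death would widen it too: if non-AAA mortality were 3–5% per annum, a figure the article does not give, about 540 events would become about 500–515.

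The required number of 616 is not shown to be wrong, and the main consequence is longer follow-up than stated. If follow-up were held to a mean of 3.5 years at the protocol's control risk, power would be about 85% for an on-treatment HR of 0.75 diluted by crossover, 91–92% for a net HR of 0.75 (530–549 events), and about 94% for a cumulative risk ratio of 0.75 with crossover. This is a planning figure to correct, not a flaw in the analysis.

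**What to change.** In Sample size {14}, recalculate the expected event total with separate risks for the two arms: the control risk, and the metformin risk after the 25% reduction and the stated drop-out and drop-in. State whether the 25% is a hazard ratio or a cumulative risk ratio, and whether it applies before or after crossover. State how 9% per annum becomes the risk at 3.5 years. The totals above are a check on that recalculation, not text to insert.

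Then choose one of two statements:

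- keep 616 events and give the longer expected mean follow-up; or
- keep a mean of 3.5 years and give the lower expected event count with its matching power.

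The abstract then needs only to agree with the choice. The cost is a change of wording plus either about 0.5–0.7 years more planned mean follow-up (on the 31–31.5% control risk) or a restated power. Enrolment and the analysis do not change.
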